## Appendix 1: Criteria defining Near-Miss (WHO)*

A woman who fulfills one of the following criteria and survives a complication during pregnancy, childbirth or in the 42 days postpartum should be considered a near-miss.

### Clinical Criteria

Acute cyanosis

Breathing rate > 40 or < 6

Oliguria unresponsive to fluids or diuretics

Loss of consciousness for ≥ 12 hours

Unconscious, no pulse/heartbeat

Jaundice concomitantly with preeclampsia

Gasping

Shock

Coagulation disorders

Cerebrovascular accident

Total paralysis

### Laboratory Criteria

Oxygen saturation <90% for > 60 minutes

Acute thrombocytopenia (<50,000 platelets)

Creatinine ≥ 300 μmol/l or ≥ 3.5 mg/dL

Bilirubin >100 μmol/l or > 6.0 mg/dL

Unconscious, presence of glucose and ketoacidosis in urine.

Lactate > 5PaO2/FiO2 < 200

pH < 7.1

### Management Criteria

Use of continuous vasoactive drug

Dialysis for treatment of acute kidney failure

Puerperal hysterectomy due to infection or hemorrhage

Cardiopulmonary resuscitation (CPR)

Transfusion ≥ 5 units of red blood cell concentrate

Intubation and ventilation for a period ≥ 60 minutes, unrelated to anesthesia*

Modified from [5]

## Appendix 2: Indicators of non-near-miss severe maternal morbidity (potentially life-threatening conditions) *

### Hemorrhagic disorders

Abruptio placentae

Placenta accreta/increta/percreta

Ectopic pregnancy

Antepartum hemorrhage

Postpartum hemorrhage

Ruptured uterus

Abortion with severe hemorrhage

### Hypertensive disorders

Severe Preeclampsia

Eclampsia

Severe hypertension

Hypertensive encephalopathy

HELLP syndrome

### Other systemic disorders

Endometritis

Pulmonary edema

Respiratory failure

Seizures

Sepsis

Thrombocytopenia <100,000

Thyroid crisis

### Management indicators of severity

Blood transfusion

Central venous access

Hysterectomy

ICU admission

Prolonged hospital stay (>7 postpartum days)

Intubation not related to anaesthetic procedure

Return to operating room

Major surgical intervention

*Modified from [5]

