For the multidimensional analysis of the repercussions of severe maternal morbidity, a concurrent cohort, specific population study will be carried out with an externally selected comparison group. The main exposure factor will be the occurrence of severe maternal morbidity (both maternal potentially life threatening or near miss conditions). During the second half of the cross-sectional study, a sample of women identified as having severe maternal morbidity will be selected and invited to participate in the longitudinal evaluation. There will be a comparison group composed of women who did not suffer severe maternal morbidity. These women will be randomly selected externally in a proportion of 1:1 from postpartum women in the rooming-in wards of the same maternity hospitals as the cases. Controls will be selected at random and balanced according to mode of delivery, maternal age and gestational age at the time of delivery.

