#### Conditions at birth

Vital status of the newborn infant as recorded on the medical chart, dichotomized into live or intrauterine death.

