#### Vitality of the newborn infant

Evaluation of the newborn infant according to 1^st ^and 5^th ^minute Apgar scores as shown on the medical chart, classified from 0 to 10.

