#### Longitudinal component

As in the cross-sectional component, women with one of the conditions indicative of severity will be selected as potential subjects for longitudinal evaluation. Once identified, research assistants who are not involved in the cross-sectional portion of the study will invite eligible women to participate in the longitudinal evaluation of the study. Women who agree to take part will be asked to sign an informed consent form and two CATI (computer assisted telephone interview) will be scheduled for 3 and 6 months postpartum plus a medical visit with the woman and the newborn infant six months following delivery.

For the control group, all women admitted to the hospital for obstetric care in the same facility on the same day on which a case has been identified and who have none of the conditions indicating severity will be eligible. Following a process of randomized selection balanced according to mode of delivery, maternal age and gestational age at the time of delivery, women in the control group will be invited to participate in the study by the research assistants in the same way as candidates to the study group. Three months after delivery, the study call center will contact the women to carry out the first step in data collection. At the time of this contact, the interviewers will again go over the objectives of the study and will apply standard questionnaires designed to investigate quality of life and postpartum depression. This interview is estimated to last around 20 minutes.

At six months postpartum, the study call center will contact the women again to carry out the second step in data collection. At this contact, the interviewers will go over the study objectives once again and apply the same standard questionnaires on quality of life and postpartum depression, lasting no more than 20 minutes. In the case of women who do not have a telephone, a reminder letter will be sent asking them to phone the study call center at the sixth month postpartum to enable the interview to take place.

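### The long-stay entry in Appendix 2 names no maternal reason, so a newborn's illness can make its mother an exposed case and open the cohort's relative risks to reverse causation

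*Protocol article*

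**What the plan says.** The Methods/Design section defines the cohort exposure broadly: "The main exposure factor will be the occurrence of severe maternal morbidity (both maternal potentially life threatening or near miss conditions"). The Longitudinal component section gives the entry rule: "women with one of the conditions indicative of severity will be selected as potential subjects for longitudinal evaluation". Controls must have none of those conditions. They are balanced with cases on mode of delivery, maternal age and gestational age at delivery.

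The conditions are listed in Appendix 2. Under Management indicators of severity stands "Prolonged hospital stay (>7 postpartum days"), with no cause attached. The next entry in that list, intubation, does carry a qualifier: it excludes intubation for anaesthesia. Under Hemorrhagic disorders stand "Ectopic pregnancy" and "Abortion with severe hemorrhage". Nothing in the article removes any of these three entries from the cohort.

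The immediate infant outcomes under Main outcomes are:
- vital status at birth, "dichotomized into live or intrauterine death";
- one- and five-minute Apgar;
- a neonatal outcome of discharge with the mother, death before 7 days, or death at 7 to 28 days.

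Infant development and growth are assessed at six months, and maternal depression and quality of life at three and six months. The Data analysis section plans relative risks for these.

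**The concern.** Exposure should come before the outcome and not be produced by it. A stay of more than 7 days after birth may be prolonged by the mother's illness or by the baby's. Where the baby is the reason, the order is reversed: the infant's condition leads to the mother's long stay, and the stay labels her as exposed.

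Apgar shows this most clearly. It is scored within minutes of birth, so in a woman who qualifies only by a later long stay it cannot be an effect of the qualifying event, but it can be an early sign of its cause. The same route reaches the six-month infant assessments. It also reaches the mother's depression and quality-of-life scores, since more than a week with a sick newborn may affect these whatever her own obstetric health.

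The control rule adds to the asymmetry, because a woman with the same stay for the same reason cannot be a control. Poorer perinatal outcome, impaired child development and more postpartum depression are all main hypotheses, so the bias falls on contrasts that the cohort is meant to test.

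**Working it through.** **The plan's own figures.** None bears on this point. The only sample-size figures are for the cross-sectional part: 75,000 × 8/1,000 = 600 near misses, as stated, and 75,000 × 140/100,000 = 105 deaths, against a stated figure of around 100. No cohort size, infant event rate or share of long-stay cases is given, so the inputs below are assumptions.

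**Inputs.**
- g: share of exposed women who qualify only by the long stay.
- p0: infant risk in controls and, with no true effect, in all other exposed women.
- m: infant risk among long-stay-only women, as a multiple of p0 (m × p0 cannot exceed 1).

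**Formula.** Exposed risk = (1 − g) × p0 + g × m × p0. Dividing by p0 gives RR = (1 − g) + g × m.

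**Results with no true effect.**

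| g | m = 0 | m = 0.5 | m = 1 | m = 2 | m = 5 |
|---|---|---|---|---|---|
| 2% | 0.98 | 0.99 | 1.00 | 1.02 | 1.08 |
| 5% | 0.95 | 0.975 | 1.00 | 1.05 | 1.20 |
| 10% | 0.90 | 0.95 | 1.00 | 1.10 | 1.40 |

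For example, g = 5% and m = 5 gives 0.95 + 0.25 = 1.20; g = 10% and m = 5 gives 0.90 + 0.50 = 1.40.

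**Which side of 1 applies to which outcome.**
- Intrauterine death: there is no living infant to keep the mother in hospital, so m may be near 0 and the RR may fall below 1.
- Early neonatal death: an infant who dies before day 7 is unlikely to prolong the stay past day 7, so m may again be below 1.
- Low Apgar, late neonatal death and six-month development: an infant ill enough to prolong the stay plausibly has a raised risk, so m is above 1 and the RR rises.
- Maternal mood: the direction is plausibly upward, but nothing in the documents allows a figure.

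**Ectopic pregnancy and abortion.** The cohort rules assume a delivery. Controls are balanced on mode of delivery and gestational age at delivery, and the six-month visit is for mother and infant. An ectopic pregnancy has no delivery, and an abortion has no counterpart among delivered controls; neither leaves an infant to assess. The vital-status outcome is defined for a newborn ("Vital status of the newborn infant as recorded on the medical chart, dichotomized into live or intrauterine death") and has no category for them. Yet both entries are eligible, and Data analysis names abortion as one of its determining-cause groups.

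**The case against.** **The entry may be narrower than it looks.** It stands under indicators of severity, within a class that Main outcomes defines as severe morbidity in the woman. Each case must record a first complication in the chain of events, and a manual of operation, not shown, standardizes diagnostic definitions. A well mother who stays for her infant arguably does not fit. This has some weight, since the silence on the reason does not mean that every reason was intended. But a research assistant screening charts against Appendix 2 meets an entry without a qualifier beside one that has a qualifier. The general definition does not settle the matter, and an unseen manual cannot be assumed to.

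**Balancing on gestational age helps.** It does, where prematurity is what prolongs the stay. It does not deal with term infants who are ill for other reasons.

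**A long infant stay is not itself an outcome category, and the bias has no fixed sign.** Both points stand, and they limit the claim. A reader might infer that the exposure list forces the perinatal relative risk above 1. The documents do not support that: the table runs from 0.90 to 1.40, and for two of the listed outcomes the pull may be downward.

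**Ectopic pregnancy and abortion.** A reader might infer that these are scored as intrauterine deaths and so inflate the relative risk heavily. Nothing in the article codes them so. The Specific objectives, Main hypotheses and Data analysis all word the infant outcomes for children born. On that denominator these pregnancies contribute no infant and leave the relative risk at 1.00 when there is no true effect. What remains is the practical gap: the women are eligible but cannot be balanced or followed up as described.

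**Conclusion.** The concern holds as an avoidable source of reverse causation. As written, the long-stay entry lets the infant's condition decide the mother's exposure status, and the control rule excludes her counterpart. The size is unknown. With 5 to 10% long-stay-only cases at five-fold infant risk, the relative risk would be 1.2 to 1.4 with no true effect; at lower multiples it is nearer 1, and for intrauterine and early neonatal death it may fall below 1. These figures rest on assumed shares and multiples and make no allowance for the dampening from gestational-age balancing. The effect on maternal mood is plausible but not quantified.

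The secondary point is one of definition: two eligible conditions have no birth, and the delivery-balanced comparison cannot accommodate them. It does not show that the infant relative risks are inflated.

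**What to change.** For the cohort only:

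1. Record the reason for any postpartum stay over 7 days, from the chart or the attending team, who are already the source for items missing from the chart. Count the stay as exposure only when the reason is maternal. Alternatively, do not accept it as the sole qualifying entry.
2. Apply the same rule when excluding controls, so that a woman kept in only by her infant's illness is treated alike on both sides.
3. At the least, repeat the relative risks without the long-stay-only cases.
4. State that the delivery-balanced comparison and the infant relative risks are limited to pregnancies ending in a birth, in line with the children-born wording. Report the maternal outcomes of women with ectopic pregnancy or abortion separately.

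Leave the Appendix 2 surveillance counts of the cross-sectional component unchanged.

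The cost is one extra item on the form, best recorded at the time, and a restriction in the cohort analysis. The downside is slightly fewer exposed women in the cohort.
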